#### Teacher training session

At each intervention school, all teachers of years 3 and 4 will participate in a one-off 45-min face-to-face training session approximately 1 week prior to implementing the ACTI-BREAK programme. The session will be conducted on school grounds at a convenient time for teachers, and will be delivered by the researcher (AW) who is a qualified and experienced primary school teacher. The training session is designed to inspire and equip the teachers with the necessary skills and knowledge to be able to implement the ACTI-BREAK programme in their classrooms. This training session will include a rationale for adding active breaks to the classroom routine, current research evidence highlighting the potential positive effect of active breaks on academic-related outcomes, explanation of the ACTI-BREAK programme and what they are required to do, and demonstrations of a range of the ACTI-BREAK activities. However, as the researcher will be delivering and observing the ACTI-BREAK programme during the first 2 weeks of implementation, extensive demonstrations of the active break activities will not be provided during the training session. At the completion of the training session, teachers will be provided with intervention materials including the ACTI-BREAK programme prompt cards, and classroom timers.

### Primary outcomes

The primary outcome of academic achievement will be assessed using measures of reading and mathematical achievement. These assessments were chosen as the primary outcomes for this study as these are the two key pillars by which teachers and schools assess academic progress [36].

#### Reading achievement

Reading achievement will be assessed using the WARP test [37]. This curriculum-based measure, designed for the Australian school context, is designed to track reading fluency of students in years 2 to 5, and involves children reading for 1 min from a 200-word passage [37]. The number of words read correctly in that minute is a measure of the student’s level of reading fluency [37]. Reading fluency has been shown to be a powerful predictor of reading performance, with meta-analytic results showing a strong correlation between curriculum-based measures of reading fluency and other standardised tests of reading performance (*r* = 0.67) [48]. The WARP test includes a set of three initial assessment passages and a set of 10 progress-monitoring passages [37]. On advice from the instrument author (personal communication), the progress-monitoring passages were chosen for the current study, as they can be expected to be sensitive to change over the 6-week intervention period. The 10 progress-monitoring passages correlate very highly to each other in terms of reading difficulty (*r* = 0.95–0.98) [49]. Thus, to eliminate potential learning effects, a different passage will be administered at baseline and end of the intervention, and is chosen based on advice from the author (personal communication). A researcher with a primary school teaching qualification and experience will administer this test individually to each student with parental consent, at baseline and during the final week (week 6) of the intervention.

#### Mathematics achievement

Achievement in mathematics will be assessed using the One-Minute Tests of Basic Number Facts, reproduced with permission from the Australian Council for Educational Research [50]. This tool consists of four One-Minute Basic Number Facts Tests [50], and is designed for the Australian school context. Each test has 33 items that focus on one of each of the following number operations: addition, subtraction, multiplication, and division [50]. This test has good test-retest reliability (0.88 to 0.94 depending on age level) [50]. To ensure alignment with the year-3 and year-4 curriculum early in the school year, and, therefore, potential to observe improvement, the subtraction test was chosen for this study. The addition test was not chosen due to the potential for ceiling effects, and thus limited potential to observe improvement. A researcher with a primary school teaching qualification and experience will administer this test to the whole class at baseline and at the end (week 6) of the intervention. Only data from students with parental consent will be used in the analyses. To accommodate class availability (e.g. due to specialist subjects) the reading and mathematics assessments will be carried out at a time that suits each classroom teacher.

### Secondary outcomes

#### On-task classroom behaviour

Information will be collected on student on-task classroom behaviour at the individual level for those students with parental consent, and at the whole class level (no identifying information will be retained). As classroom behaviour can vary as a function of time of day, each class teacher will be required to record all observations of classroom behaviour at a consistent time each day. However, due to differing timetables across classes and schools, it will not be possible for all teachers to record behaviour observations at the same time of day.

Teachers at intervention and control schools will be required to observe behaviour during a 10-min observation period during a seated lesson at three time points at baseline and again at the end (week 6) of the intervention. In addition to baseline and the end of the intervention observations of behaviour, teachers at intervention schools will be required to record observations of behaviour during a 10-min observation period immediately before and immediately after participation in an ACTI-BREAK at three time points during week 3 of the intervention. This pre-post measure will enable the acute effect of active breaks on classroom behaviour to be explored. Teachers will record observations of individual and group classroom behaviour simultaneously in order to limit the number of times that teachers will be required to record observations. Teachers will be given a record sheet with student names pre-filled, and each observation will take only a few seconds to complete. Given this, and as teachers continually monitor classroom behaviour as part of their daily routine, this approach is considered feasible. Lastly, teachers’ reports of classroom behaviour as reported in a similar previous study were shown to be reliable (alpha = 0.85) [18]; however, to the authors’ knowledge only one previous study has used such measures. Nonetheless, although the same class teachers who deliver the intervention will also record observations of behaviour, risk of bias is expected to be minimal.

Classroom behaviour at the individual level will be measured by teachers using a tool adopted from the Direct Behaviour Rating Scale [51]. The Direct Behaviour Rating Scale is a hybrid of direct observation and behaviour rating scales. This observation tool requires teachers to indicate for each child, on a scale from 1 (0%) to 10 (100%), the percentage of time that they are on-task, referred to as academically engaged in this tool (i.e. listening to the teacher, writing, looking at instructional materials, etc.) during the observation period. This tool provides a valid measure of classroom behaviour, when compared with direct observation (*r* = 0.81 to 0.87) [52]. Further, this tool has evidence of reliability (*r* = 0.91) based on data from 617 primary school students obtained from 44 classroom teachers [51].

Behaviour at the whole class level will be measured using a modified version of the Classroom Behaviour and Assets Survey-Teacher which is designed to efficiently provide a snapshot of the teacher’s perception of the behaviour of a whole class of students [53]. Teachers will be required to indicate the proportion of the class displaying on-task behaviour (as defined in the individual behaviour assessment tool), during the observation period. Response options include: 0 (0 students), 1 (1–2 students), 2 (a few students), 3 (about a quarter of the class), 4 (about half of the class), 5 (about three quarters of the class), 6 (most of the class), and 7 (all of the class) [53]. Although few tools are available for assessing classroom behaviour at the classroom level, and information on reliability and validity is lacking, a modified version of this tool has been used in a similar study, with evidence of reliability (alpha = 0.85) [18].

#### Physical activity

Waist-worn ActiGraph GT3-X accelerometers (children with parental consent) will be used to provide an objective measure of children’s moderate- to vigorous-intensity physical activity across the school day. The ActiGraph accelerometer is commonly used in studies involving children [54] and has documented evidence of validity and reliability for measuring children’s physical activity [55]. Accelerometers will be worn during waking hours for seven consecutive days at baseline, mid-intervention (intervention group only), and the end (week 6) of the intervention period. Measures will be taken in the last week of the intervention, rather than post intervention as the intervention is intended to have acute effects.

The accelerometers will be distributed and collected from the child’s school at the beginning and end of each 7-day wear period. The researcher will explain about, and fit the monitors to children with parental consent and provide children with an information leaflet to take home to their parents explaining when and how the monitor should be worn and care instructions. Participants’ physical activity will be included for analysis if they wear the accelerometer for at least five school hours on at least one school day, as used in similar studies, involving physically active lessons [23]. Freedson cut-points will be used to classify physical activity as moderate- to vigorous-intensity [56]. These cut-points have been shown to accurately classify children’s moderate- to vigorous-intensity physical activity (ROC-AUC = 0.90) [57]. Data will be collected in 15-s epochs [58] and non-wear time will be defined as 20 min of consecutive zero’s, as commonly used in studies involving children [59].

### Intervention fidelity

To assess fidelity of implementation, children will wear accelerometers mid-way through the intervention (week 3) as well as during the final week of the intervention period (week 6). Furthermore, teachers will complete a log of the ACTI-BREAKS that they complete over the intervention period. The researcher (AW) will collect these at the end of every week to ensure teacher fidelity throughout the study. Accelerometer data will be compared with teacher logs of ACTI-BREAKS completed at week 3 and week 6 of the intervention to verify that students were physically active at a moderate intensity for the 5-min ACTI-BREAK duration.

### Process evaluation

Subjective evaluations of the intervention components will also be provided by students and teachers throughout the intervention. During each of weeks 1, 3, and 6 of the intervention, students will be asked to rate three different ACTI-BREAK activities (decided by the classroom teacher), immediately following participation using a 4-point Likert scale ranging from ‘I hated it’ = 1 to ‘I loved it’ = 4. Upon competition of the 6-week programme, students will be asked to complete a questionnaire to rate how they feel about the ACTI-BREAK activities using a 4-point Likert scale with responses ranging from ‘strongly disagree’ = 1 to ‘strongly agree’ = 4 in the areas of (1) enjoyment, (2) effect on learning and behaviour, (3) ability to do the activities, and (4) preferred duration, intensity, and frequency of activities. For example, ‘I enjoyed the ACTI-BREAK programme’ and ‘I found it easier to concentrate after doing ACTI-BREAK activities’. Students will also have the opportunity to provide additional feedback on the following open ended questions: ‘What did you like about the ACTI-BREAK programme?’ and ‘Was there anything you didn’t like about the ACTI-BREAK programme?’

Post-intervention focus groups will also be conducted with students, facilitated by the researcher. The focus groups will be recorded and later transcribed, with participant consent. Specifically, the questions asked will be designed to provide a more in-depth insight into topics covered in the questionnaire. For example, students will write down the names of two of their favourite, and two of their least favourite ACTI-BREAK activities, and then explain what they liked or did not like about the particular ACTI-BREAK, and what they would change.

A one-on-one 30- to 45-min telephone interview will be conducted with the teachers involved in the intervention group, after programme completion. The researcher will conduct these interviews which will be recorded and transcribed. The interviews with teachers will be designed to identify barriers and facilitators to implementation of ACTI-BREAKS, as well as strengths and weaknesses of the programme. The following types of questions will be asked, for example: ‘Were there any ACTI-BREAKS you thought worked particularly well/didn’t work particularly well?’ and ‘Was there anything that made it difficult for you/helped you to use the ACTI-BREAK programme?’

### Data analysis

All statistical analysis will be conducted using Stata 14.0. Multilevel mixed-effects linear regression models will be used to assess the impact of group (intervention vs. control) on achievement scores in reading and mathematics, mean per cent of time in on-task behaviour, and physical activity level at the end of the intervention, each adjusted for baseline levels of the corresponding variable and clustering by class. All analyses will control for physical activity levels at baseline. The fixed effect of school will be added to the model to account for the unit of randomisation. All analyses will be stratified by sex. Alpha levels will be set at *p* < 0.05. As this is a pilot study, the intervention will not be adequately powered to detect small changes between groups. Instead, trends in associations will be investigated. Analyses will be conducted both on the intention-to-treat approach, and per protocol analysis (using data from fidelity checks).

Process evaluation data from focus groups and interviews will be analysed using Braun and Clarke’s six phases of thematic analysis [60]. Codes will be generated, and continually revised throughout the analysis process. Following coding of the transcripts, themes will be identified and defined. These data, along with data obtained from student enjoyment and satisfaction questionnaires, will provide information that can be used to improve the programme for future testing.

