### Power calculation

The detectable difference, based on grade-based benchmarks for year-3 reading scores in the Wheldall Assessment of Reading Passages (WARP) test [37] at mid-year, and 12 clusters (classes) per group, each with nine students, is 23.55 points in reading achievement with power set to 80%. Based on results from this study effect sizes will be generated to inform the sample size needed for a full-scale trial.

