### Study setting

Government primary schools located within a 30-km radius of Deakin University and with a Victorian Socio-economic Indexes for Areas (SEIFA) Index of relative socio-economic advantage and disadvantage deciles of 4, 5, or 6, representing middle socio-economic position (SEP) will be invited to participate. Middle SEP government schools were chosen for this study as children attending these schools represent a large number of primary school children in Australia, making results likely to be generalisable to a large number of schools and children. Students attending Victorian government schools spend approximately 6.5 h per day at school (9.00 a.m. to 3.30 p.m.), and have a short recess/snack break (approximately 30 min) and a longer lunch break (approximately 1 h). The intervention will target year-3 and -4 classes (aged approximately 8–10 years). For schools to be eligible, they must have straight or composite year-3 and year-4 classes. Schools where composite classes mixed year-3 and year-4 students with other grades (e.g. years 2/3 or years 4/5 composites) were not eligible. Based on a 37% response rate (as demonstrated in a similar study conducted in the Australian school context [38]) and an average class size in Victorian schools of 23 students per class [39], we anticipate that nine students per class will consent to take part in this pilot study. For feasibility reasons, the intention is to recruit six schools (three intervention and three control) from which a sample size of 216 children is estimated (six schools × four classes (two classes per year level) [40] × nine students).

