### Randomisation

Schools will be randomised at the school level (to avoid potential for contamination) to either the intervention or waitlist control group, prior to baseline assessments. The waitlist control group will be provided with the intervention materials after the final data collection period. Randomisation will be carried out via computer-generated random number sequence by a researcher who has no contact with the schools or participants. As all schools will be from middle socioeconomic position areas within a similar geographical location, it is unlikely for there to be large differences in baseline characteristics, including academic achievement levels. Any differences between the intervention and control groups will be by chance [41], and adjusted for in the analyses.

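### The Randomisation section promises adjustment for whatever differs between groups, which does not match the set model in Data analysis; year level is also missing from that model, at a small cost in precision

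*Protocol article*

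**What the plan says.** The Data analysis section specifies multilevel linear models for the group effect on each outcome at the end of the intervention, "each adjusted for baseline levels of the corresponding variable and clustering by class". It also controls all analyses for baseline physical activity, adds school as a fixed effect and stratifies by sex. Year level does not appear.

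The Randomisation section argues that large baseline differences are unlikely because the schools are alike, and then states: "Any differences between the intervention and control groups will be by chance [41], and adjusted for in the analyses". It gives no variable list, threshold or procedure, and Data analysis does not refer back to it.

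The Study setting section builds the sample from "six schools × four classes (two classes per year level) [40] × nine students". Eligible schools are described this way: "they must have straight or composite year-3 and year-4 classes". Year level is therefore a planned feature of the sample. It is usually a property of the class, but it varies between children within a composite class. The Power calculation also depends on year level, since it is "based on grade-based benchmarks for year-3 reading scores in the Wheldall Assessment of Reading Passages (WARP) test".

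**The concern.** The first issue is that two sections give different instructions for the same models. One lists the covariates and the other makes the list depend on what the baseline data show. Two analysts who both follow the article could fit different primary models. The Randomisation section itself attributes any differences to chance, and chance imbalance is not a reason to choose covariates after seeing the data. The Power calculation section says effect sizes from this pilot will inform the sample size of a full trial, so those estimates should come from one model fixed in advance.

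The second issue is that year level is known for every child and could plausibly relate to reading, arithmetic, behaviour and activity. In straight classes, any year-3/year-4 difference left after baseline adjustment enters the class variance. With year level balanced, that makes the reported standard error too large. With an uneven year mix, it adds real error to the estimate. What matters is how much difference is left.

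**Working it through.** **Plan's own figures.** The sample size reproduces: 6 × 4 × 9 = 216. The detectable difference ("12 clusters (classes) per group, each with nine students, is 23.55 points in reading achievement with power set to 80"%) can be neither reproduced nor refuted, because no SD or intraclass correlation (ICC) is given. Taking alpha as two-sided 0.05 ("Alpha levels will be set at *p* < 0.05" does not state sidedness):

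23.55 = (1.960 + 0.842) × SD × √(2 × (1 + 8 × ICC) / 108)

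This implies an SD of 61.8 at ICC 0, 46.0 at ICC 0.10 and 33.5 at ICC 0.30. The article therefore supplies no SD that would put a year gap on the word scale.

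**1. The two covariate rules side by side.** Data analysis gives a finite list. Randomisation gives a class of covariates defined by the observed data. They coincide only if the differences to be adjusted for are confined to the baseline score and baseline physical activity, and the Randomisation wording has no such limit.

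**2. What an open rule can do.** Simulation under the null, with six independent school means (three against three), a school-level t test and independent candidate covariates (all assumed):

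| Way of choosing | Type I error |
|---|---|
| Always adjust for the most imbalanced candidate | about 5% |
| Free choice among the unadjusted and single-covariate models, 4 candidates | about 14% |
| Same, 6 candidates | about 17–18% |

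A mechanical rule does little harm. The last two rows are worst cases, in which the most favourable model is reported. The article does not say which of these would apply. If such covariates were school-level, each would also use one of the 4 between-school degrees of freedom: critical t goes from 2.78 (4 df) to 3.18 (3 df) or 4.30 (2 df).

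**3. Cost of omitting year level under the planned baseline adjustment.** Simulation of 24 classes of nine children, two year-3 and two year-4 classes per school. Assumptions: year gap 0.3, 0.6 or 0.9 SD, the same at baseline and follow-up; ICC 0.05–0.15; baseline–follow-up correlation r of 0.7 or 0.9. The article's reliabilities serve as proxies for r: 0.88–0.94 for mathematics (test-retest) and 0.95–0.98 for reading (between passages). The school fixed effect was left out because, with intercept and group, the design has 7 columns but rank 6, so the group effect could not otherwise be estimated. That is a separate matter.

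| Model | SE of group effect, year omitted / included |
|---|---|
| Baseline-adjusted (planned), r = 0.9 | 0.99–1.01 |
| Baseline-adjusted (planned), r = 0.7 | 1.00–1.04 |
| No baseline adjustment (not the plan) | 1.05–1.56 |

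These ranges combine class-mean regressions with child-level mixed models. The mixed models used few replicates, so differences of about 1% are within simulation noise. The reason for the small effect is direct: a raw gap g leaves at most about g × (1 − r) after baseline adjustment. For g = 0.9 SD that is 0.09 SD at r = 0.9 and 0.27 SD at r = 0.7.

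**4. When the loss would be larger.** Assume a class SD of 5 words and a child residual SD of 21. The class-mean variance is then 5² + 21²/9 = 74. A gap d that remains after baseline adjustment adds d²/4 when classes are straight, so the SE ratio is √((74 + d²/4)/74):

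| Remaining gap d (words) | 3 | 6 | 10 | 15 |
|---|---|---|---|---|
| SE ratio | 1.015 | 1.059 | 1.157 | 1.327 |

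If a gap of 10 or 15 words were left over from imperfect adjustment at slope 0.9, the raw gap would have to be 10/0.1 = 100 or 15/0.1 = 150 words, on a 200-word passage. Otherwise the two years would have to differ by 10–15 words in six-week gain. In evenly mixed composite classes the added variance is (d²/4)/9 = d²/36, and the ratios at 10 and 15 words fall to 1.02 and 1.04.

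With an uneven year mix (one to three year-4 classes per school, school SD 3, all assumed), the true SD of the estimate was 4.61 without year level against 4.33 with it at a 10-word gap, and 4.96 against 4.35 at 15 words.

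**The case against.** The best defence is that the Randomisation clause only points forward to Data analysis. The sentence before it mentions baseline academic achievement, and the models do adjust each outcome for its own baseline and for baseline activity. No imbalance test or selection procedure is stated, and a full covariate list is commonly left to an analysis plan, which is not shown. This narrower reading is possible. But the clause covers any differences without limit, so the mismatch lies in the article's own text and is not a missing detail. A reader might go further and infer that nominal p-values are invalidated. The documents do not support that: no selection procedure is stated, and a mechanical rule keeps the error rate near 5%.

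On year level, the defence largely succeeds. A reader might infer from the omission that standard errors are inflated by 16–33%. That needs a 10–15 word gap remaining after baseline adjustment, and nothing in the article gives a year-4 score, a year gap or gains by year. Baseline adjustment carries most of any gap, and the plan has two classes per year level in every school, so no material bias is expected. What remains is that planned balance is not guaranteed in the analysed sample, with about nine of 23 children per class expected to consent and composite classes eligible. No baseline–follow-up correlation is given for on-task behaviour or physical activity.

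The pilot also says it is not powered for small changes and will look at trends. That lowers the stakes, but it does not settle which model produces the effect sizes.

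**Conclusion.** The point stands mainly as an inconsistency between sections. The open adjustment promise in Randomisation does not match the set model in Data analysis and, read literally, leaves covariate choice to the observed data. With three schools per arm it would almost certainly come into play. The harm depends on how it is applied, from negligible under a mechanical rule to a type I error of about 14–18% in the worst case simulated.

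The omission of year level is real but minor. The standard error changes by about 0–4% under the assumed year gaps and ICCs, and by about 1% or less at the reported correlations, taken as proxies. With year level balanced, the estimate itself is essentially unaffected. The loss could be larger only if six-week gains differ by year, if the year mix is uneven, or for outcomes more weakly correlated with baseline. The ratios of 1.16 and 1.33 are worst-case scenarios on assumed inputs. Adding year level is an inexpensive improvement, not the correction of a serious error.

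**What to change.** In the Randomisation section, replace the closing clause with a reference to the covariates named in Data analysis, and state that no adjustment will be chosen from observed baseline differences. In Data analysis, present the covariates as a closed set fixed before data are seen, and add child year level (3 or 4) as a fixed effect in every outcome model. Entering it for each child, not for each class, handles composite classes.

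The cost is about one sentence in each section and one degree of freedom at child or class level. Year level is already known for every child, so no extra data collection is needed.

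### School entered as a fixed effect in a school-randomised trial leaves the intervention effect inestimable in the primary model

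*Protocol article*

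**What the plan says.** Under Randomisation, the protocol article allocates whole schools: "Schools will be randomised at the school level (to avoid potential for contamination) to either the intervention or waitlist control group, prior to baseline assessments". Control schools receive the materials only after the last data collection, so no school changes arm within the analysed data. Under Study setting, "the intention is to recruit six schools (three intervention and three control) from which a sample size of 216 children is estimated", laid out as "six schools × four classes (two classes per year level) [40] × nine students".

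Under Data analysis, one family of mixed linear models serves reading, mathematics, on-task behaviour and physical activity. Each regresses the end-of-intervention value on group, "each adjusted for baseline levels of the corresponding variable and clustering by class", with baseline physical activity as a further covariate. The section then adds: "The fixed effect of school will be added to the model to account for the unit of randomisation". Results are to be stratified by sex and produced by intention to treat and per protocol. The article nowhere describes a random school effect or a model without the school term.

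**The concern.** A fixed effect for school absorbs every difference between schools. In a trial that randomises schools, the intervention effect is itself a difference between schools, so nothing is left from which to estimate it. The sentence is meant to respect the unit of randomisation, but it has the opposite effect.

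Two things are at stake. First, the reported effect would be missing, or would be a contrast between two schools picked by the coding. Under Power calculation, the article says that effect sizes from this pilot will be used to size the full-scale trial, so a meaningless estimate would carry forward. Second, with class as the only random effect, any standard error reported ignores variation between schools, which is the variation that randomising schools makes relevant.

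**Working it through.** **Inputs from the article.** 6 schools, 3 per arm, 4 classes per school, 9 children per class. The class size comes from 0.37 × 23 = 8.51, rounded to 9. The stated total reproduces: 6 × 4 × 9 = 216. There is one outcome time, with fixed terms for group, school, baseline outcome and baseline physical activity, and clustering by class. The article gives no SD or ICC, so every ICC below is an assumption.

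**Step 1: estimability (no assumption needed).** Let G be the group indicator and S1 to S3 the indicators of the three intervention schools. For every child, G = S1 + S2 + S3.

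| Fixed part | Columns | Rank |
|---|---|---|
| Intercept, group, 5 school indicators | 7 | 6 |
| The same plus two baseline covariates | 9 | 8 |
| Intercept, group, two baseline covariates (no school term) | 4 | 4 |

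In the first two rows the group coefficient is not estimable. A random class effect leaves the fixed-effects columns unchanged, so it cannot help. The same holds within each sex stratum as long as every school contributes children.

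**Step 2: what would be reported.** If software drops a further school indicator, one intervention school and one control school are left as references, and the group coefficient is their difference. The other four schools enter only through the covariate slopes and the class variance. There are 3 × 3 = 9 possible pairs. In one simulated data set (true effect 5, SD 40, school and class ICC 0.05 each, all assumed), the coefficient ran from 0.4 to 26.1 across the nine pairs. If software drops group instead, there is no estimate.

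**Step 3: error rate of that coefficient.** Take total variance 1, school ICC ρs and class ICC ρc = 0.10, with no further covariates.

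- Variance of a class mean within a school: v = ρc + (1 − ρs − ρc)/9.
- Variance the model assigns to a two-school difference: 2v/4.
- True variance under no effect: 2v/4 + 2ρs.
- Ratio: R = 1 + 4ρs/v.
- The class variance is estimated on 6 × (4 − 1) = 18 df, so the error rate against the large-sample cut-off is P(|t18| > 1.96/√R).

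Example, ρs = 0.05: v = 0.10 + 0.85/9 = 0.1944, R = 1 + 0.20/0.1944 = 2.03 and 1.96/√2.03 = 1.376, which gives 18.6%.

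The first two rows of the next table come from the formula. The rest come from 40,000 simulated null trials per scenario.

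| Analysis, nominal 5% | ρs = 0 | 0.02 | 0.05 | 0.10 |
|---|---|---|---|---|
| Two-school group coefficient, cut-off 1.96 | 6.6% | 11.6% | 18.6% | 28.2% |
| The same, t on 18 df | 5.0% | 9.3% | 15.8% | 25.0% |
| School term dropped, class only, cut-off 1.96 | 6.4% | 10.1% | 15.0% | 20.8% |
| School-level t test, 4 df | 5.0% | 5.0% | 5.0% | 5.0% |
| School-level statistic, cut-off 1.96 | 12.2% | 12.3% | 12.0% | 12.3% |

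Simulating the first row gives 6.6%, 11.6%, 18.8% and 28.4%. The last row agrees with P(|t4| > 1.96) = 12.2%.

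**The case against.** **A slip of wording.** The strongest defence is that fixed was written for random, since the stated purpose fits a random effect. That may be so, but the text names a specific model and nothing else in the article corrects it. If it is a slip, the sentence still has to change.

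**A pilot looking for trends.** The article concedes limited power, and its feasibility and process results do not depend on this model. That narrows the damage. It does not remove it, because the planned use of the effect sizes needs a valid point estimate.

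**Limits on the numbers.** Four points stand.

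- The two-school contrast is one of two outcomes. If school is entered first, group may be dropped instead. The article adds school to a group model, which makes the contrast the likelier result, but it fixes no order of terms.
- The inflated error rates come from leaving school variance out of the standard error, not from the arbitrary choice of schools. A three-against-three average under fixed school effects has model variance 2v/12 and true variance 2v/12 + 2ρs/3. That is the same ratio R and the same error rates.
- Part of the inflation is the 1.96 cut-off. At school ICC 0 it accounts for all of it.
- The 12% figure applies to school-level summaries judged against 1.96. For a random-intercept model judged against 1.96, with school variance truncated at zero, the rates are about 5%, 7%, 9% and 10.5% in the four scenarios.

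**Conclusion.** The plan is wrong as written and must be corrected before analysis. As specified, the model cannot estimate the intervention effect for either primary outcome or for the secondary outcomes that share it. That conclusion is algebraic: it follows from whole-school allocation, one outcome time and a fixed school effect, and it needs no SD, ICC or effect size.

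The error rates show the second fault, the missing school variance. They rest on assumed ICCs and the planned balanced layout. At a school ICC of 0.05 the nominal 5% test runs at about 19% for the leftover coefficient. Deleting the school term alone still leaves about 15%, so deletion is not a remedy.

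**What to change.** Replace the sentence on the fixed effect of school with one of these:

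1. A random intercept for school and a random intercept for class nested in school, with the group effect tested on Kenward-Roger or Satterthwaite degrees of freedom (about 6 − 2 = 4).
2. A t test on 4 df comparing the baseline-adjusted means of the three intervention and three control schools.

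The second is the safer choice with six schools. In the four simulated scenarios the school variance was estimated as zero in 57%, 41%, 26% and 14% of trials, so a mixed-model correction cannot be relied on to return about 4 df. If the first is chosen, state in advance what will be done when that happens. Rule out large-sample z tests in either case.

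The change itself is one sentence of text and one line of code. Recruitment, delivery and measurement are untouched. Intervals widen: the critical value on 4 df is 2.78 rather than 1.96, and school variance is now counted.

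The Power calculation section treats 12 classes per group as the clusters, so its detectable difference of 23.55 points should be restated at school level. The size of the change depends on ICCs that the article does not give. With class ICC 0.05 and school ICC 0.02, 0.05 or 0.10 (assumed), the difference detectable with 80% power on 4 df is about 0.74, 0.91 or 1.13 SD. A class-level calculation at the same total ICC gives 0.48, 0.51 or 0.57 SD.
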